### **Secondary Objectives:**

1. To study the effect of c-KMC on prevalence of mild depressive symptoms (PHQ 9 score 5-9) and suicidal ideation in mothers in postpartum period.
2. To study the effect of c-KMC in LBW infants during the neonatal period on successful breastfeeding performance (measured by IBFAT score), complete lactation failure, perceived breast milk insufficiency and use of breast milk substitutes;
3. Association of Gut inflammation (Fecal Neopterin, Myeloperoxidase,  $\alpha 1$  antitrypsin) in neonatal period with linear growth in the first 6 months of life.

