## **Outcomes**

### **Primary**

1. Infant breast milk intake during the neonatal period
2. Moderate to severe maternal postpartum depressive symptoms (Patient Health Questionnaire-9 score  $\geq 10$ ) and salivary cortisol levels at the end of neonatal period
3. Gut inflammatory markers: Fecal Neopterin, Myeloperoxidase,  $\alpha 1$ -antitrypsin at baseline and at the end of neonatal period

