2 members i.e. a supervisor trained in biological sample collection, (including saliva and stool), and a field worker to help during sample collection and interviewing. A Coordinator will ensure and coordinate all sample collection, as well as storage and transport of samples. Training is provided to the Supervisors for the interviews with the PHQ 9(19) and breastfeeding assessment questionnaire(40).

Anthropometry measurements (length and weight) infection ascertainment will be done when the babies are 1, 3 and 6 months of age as a part of the main intervention trial.

Non-invasive stable isotope methodology (deuterium oxide $^2\text{H}_2\text{O}$  technique) will be used to assess infant milk intake. This allows for accurate and non-invasive data acquisition and overcomes previous methodological issues associated with infant weighing (41, 42). Infant breast milk intake measurement will be done using salivary samples from the mother and baby collected sequentially over a two-week period starting from the day of enrolment to get correct estimates as by this time milk production usually reaches optimal levels (43). Lactating women will be given an oral drink containing 30g of  $^2\text{H}_2\text{O}$  at enrolment. Saliva samples will be collected at baseline (day of enrolment), day1, 3, 7, 13 and 14 after enrolment using sterile cotton swabs. Saliva samples will be stored in a cool box by trained field workers and transported to the storage facility within 6-8 hours. This will be stored in the  $-20^\circ\text{C}$  freezers in the Central Research Laboratories - Society for Applied Studies (CRL-SAS), Devli until analysis as per International Atomic Energy Agency (IAEA) guidelines(41). The samples will be shipped in batches on dry ice to St. John's Research Institute, Bangalore, for analysis within 6-12 months of collection. The appearance and subsequent disappearance of  $^2\text{H}_2\text{O}$  will be analyzed by enrichment of  $^2\text{H}_2\text{O}$  in mother and baby saliva samples using the Fourier transform infrared (FIR) spectrophotometry. The infant breast-milk intake will be expressed as the area under the curve over this 14 day period; this will help us to take into account the day-to-day variability of the breast milk intake.

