Breastfeeding performance will be assessed using the validated IBFAT breastfeeding assessment tool (40) which is based on 4 parameters i.e. readiness to feed, rooting, fixing (latch on) and sucking. Higher score denotes better breastfeeding. Lactation failure, perceived breast milk insufficiency and use of breast milk substitutes during the neonatal period (enrolment to day 28) will be assessed by interviewing mothers with a semi-structured questionnaire on day 29 adapted from WHO/UNICEF resource material on breastfeeding counseling and UNICEF breastfeeding assessment tools (<https://www.unicef.org.uk/babyfriendly/baby-friendly->

[resources/guidance-for-health-professionals/tools-and-forms-for-health-professionals/breastfeeding-assessment-tools/](#)).

Assessment of depressive symptoms in mothers will be done at the end of the neonatal period i.e. day 28 of life, by the trained OM team using the validated PHQ-9 questionnaire which is also pre-tested (19). For maternal salivary cortisol determination which is being used as an indicator of stress, fasting salivary samples will be collected by placing cotton swab in the oral cavity of the mother in the morning around 7-8 am when the baby is 28 days old. The morning salivary sample at 7- 8 am is seen to correlate with the entire area under curve of the awakening response of cortisol and even a single sample per participant could assess whether a mother had lower or higher concentration of cortisol (44). As the cortisol levels may also vary in relation to breastfeeding (45), we will collect two salivary samples from each mother and baby in the morning (around 8 am) before and after breastfeeding when the baby is 28days old. The time of salivary sample collection and previous breastfeeding will be noted. The samples will be aliquoted, labeled and transported in cold boxes to the storage facility at CRL-SAS, Devli within around 8 hours where it will be stored in -20 °C in freezers until further analysis. Analysis will be done in CRL-SAS using quantitative ELISAs. The kits will be validated in our lab prior to testing of study samples. We also plan to collect saliva samples from the infant at day 28 as an exploratory exercise to study relationship of infant stress with maternal stress and its association with milk intake, though it is not a part of our primary objectives.

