For stool collection, mothers will be provided with a cold box with 4 ice packs and sterile stool container at the day of enrolment and on Day 28 by the study workers. To ensure the cold chain the family will be asked to keep 2 gel/ice packs in the cold box and 2 in a freezer in their home (for families who have a refrigerator) or in a nearby home or shop. They will be asked to change the gel packs in the ice box after about 12 hrs. The worker will educate the mother about stool collection using the spoon following aseptic precautions in the sterile stool vial. Around 5-10g of stool sample (1 to 2 spoon) will be collected. After stool collection in the vial, the vial is to be placed in the cold box with all the 4 ice packs. The caregiver/ mother will be instructed to collect stool samples only when the infant passes stool between 6am to 3pm (noon) because of operational feasibility and prompt transportation of the samples on the same day. The mother will be provided with a phone number to inform the study team as soon as possible after stool collection. Alternatively, the field worker will also call the family intermittently to get confirmation on stool collection. A maximum wait time of 3 working days will be allowed to get stool specimen

of each infant at each time point. After telephonic confirmation of stool collection, the field worker will visit and collect the stool specimen with the cold box from home. Collected stool samples will be transported from the home to the field office at Palwal within 3-4 hours where it will be stored in the refrigerator (2-8 degrees). At the end of each day (i.e. 8-10 hours of sample collection) the samples will be transported in cold boxes to the storage lab where the samples will be stored at -80°C till further analysis. Analysis of the gut biomarkers will be done using commercially available ELISA kits at Clinical and Research Laboratories, Devli, New Delhi. A fully automated ELISA Evolis Twin Plus (Biorad) system will be used. All the kits will be validated in our lab prior to testing of study samples. Gut microbiome analysis(not necessarily a part of the PhD), will be done in Center for Human Microbial Ecology (CHME) laboratory in Translational Health Science and Technology Institute ([http://www.thsti.res.in/chme/about\\_chme.php](http://www.thsti.res.in/chme/about_chme.php)).

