infant breast milk intake, gut inflammation, multivariable linear regression models will be used. Covariates identified as potential confounders will be included in the regression models for adjustment. Regression analysis will also be done to examine the effect of infant milk intake, postpartum depressive symptoms and gut inflammation on linear growth velocity (birth to 3 months and 3 to 6 months) and LAZ scores of the LBW infants. To assess dose-response relationships between duration of KMC and volume of breast milk output generalized additive models shall be used. We may also use Instrumental Variable analyses to study associations between actual intensity of SSC and Breast feeding and the outcomes of the proposed studies.

For qualitative outcomes e.g. mothers with PHQ9 score  $\geq 10$ , lactation failure, perceived milk insufficiency, proportions will be reported. If necessary to adjust for any baseline differences, univariable and multivariable logistic regression analysis or analyses with generalized linear models of the binomial family with a log link shall be done to estimate the impact of KMC on these outcomes. Potential interaction between cKMC and all other variables on the outcome measures will be examined by including interaction terms in the multivariable regression models, after identifying subgroup differences by simple stratified analyses. In order to quantify biologic interactions(52) we will estimate the relative excess risk due to interaction(RERI) with its 95% CI(53, 54).

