**Process for PHQ-9 assessments**

- **Tool:** Validated PHQ 9 questionnaire (hindi version). This was the same hindi form that was pre-tested and used in one of our previous studies.
- **Process:** Assessment was done at home by an independent team at the *end of neonatal period* i.e. day 28 (window period was +7 days) (Though the workers are part of the intervention delivery team, it was ensured that the workers assessed PHQ9 in mothers belonging to a different area (PHC) where they were not involved in intervention delivery so that the observations are independent.) If door was locked or the mother was unavailable and her date of availability was uncertain, she / family was contacted either by home visit or phone for at least 3 times within the window period.
- **Training:** Workers were trained to conduct interview for PHQ 9 and fill the PHQ 9 questionnaire following the KMC-GCC form filling guidelines. The workers were reassessed and retrained by a faculty of the department of clinical psychology of AIIMS, New Delhi. The PI, Coordinators were also trained for assessing PHQ 9. Training logs are maintained.
- **Quality checks:** The PI of the study conducted random visits in 1-2% of the PHQ 9 assessments and checked whether the PHQ 9 scores matched when scored independently. Also around 2% of the interviews are being recorded after taking consent for recording.
- **Advise for consultation:** All Mothers, irrespective of any group, who are having scores  $\geq 10$  were advised to consult a nearby physician at the earliest for further advise. A standard message is given to the family. Facilitation was done wherever possible.

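### PHQ-9 and stool markers taken at day 28 are related to length velocity from birth to 3 months, when about a third of that interval has already passed

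*Combined protocol and SAP*

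**What the plan says.** Under Description of the PhD sub-study, the Data analysis paragraph proposes regressions to study an "effect of infant milk intake, postpartum depressive symptoms and gut inflammation on linear growth velocity (birth to 3 months and 3 to 6 months"; LAZ is a further outcome, at an age it does not give. Growth is the outcome; the other three are the exposures. The timing is set elsewhere:

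- **Depressive symptoms.** Protocol: "Assessment of depressive symptoms in mothers will be done at the end of the neonatal period i.e. day 28 of life". The SAP (Process for PHQ-9 assessments) gives "day 28 (window period was +7 days".
- **Gut markers.** The primary outcome is listed "at baseline and at the end of neonatal period". Families receive a "sterile stool container at the day of enrolment and on Day 28 by the study workers", and the protocol adds: "A maximum wait time of 3 working days will be allowed to get stool specimen". The Data analysis paragraph does not say which sample enters the growth regression.
- **Length.** Measured at screening, within 72 hours of birth. Later anthropometry "will be done when the babies are 1, 3 and 6 months of age as a part of the main intervention trial".
- **Growth outcomes.** The secondary outcomes list velocity over birth to 3 months and 3 to 6 months, and LAZ at 1, 3 and 6 months. No 1-3 month velocity is defined.

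Secondary objective 3 is an association of gut inflammation "in neonatal period with linear growth in the first 6 months of life". Adjustment is for potential confounders that are not named. The Introduction and Theoretical Framework concede that causality may be hard to establish, but say nothing about time order. The SAP covers only depressive symptoms and cortisol and contains no growth analysis.

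**The concern.** A measurement at day 28 cannot be placed before growth in the four weeks leading up to it. An infant who grows poorly in month 1 may have a more distressed mother, or may have an illness that also inflames the gut. Either route links the day-28 measure to birth-to-3-month velocity even if the measure has no bearing on later growth. The plan calls the result an *effect*.

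The plan's own rationale makes this matter. The Theoretical Framework (item C) justifies the faecal markers as possible predictors of growth faltering that comes afterwards, and describes malabsorption, malnutrition and poor growth as feeding one another. The first point calls for growth after the marker; the second makes a two-way relation plausible. The framework also expects KMC to act on maternal depression, on gut inflammation and on linear growth, so arm could be a common cause, yet it is not named for these models.

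What is at stake is the growth half of planned article 3 and the explanatory models that the sub-study is meant to support.

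**Working it through.** The plan gives no figure for this point, so there is none to reproduce.

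**1. Share of the interval before measurement.** Share = age at measurement / length of the interval. The documents do not state 3 months in days, so 84, 90 and 91.3 are all shown.

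| Measurement | Day | /84 | /90 | /91.3 |
|---|---|---|---|---|
| PHQ-9 or stool, on schedule | 28 | 33% | 31% | 31% |
| Stool after a 3-day wait | 31 | 37% | 34% | 34% |
| PHQ-9 at end of window | 35 | 42% | 39% | 38% |
| Milk intake, end (enrolment at day 4-7, plus 14 days) | 18-21 | 21-25% | 20-23% | 20-23% |
| Baseline stool | 4-7 | 5-8% | 4-8% | 4-8% |

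For 3-6 month velocity the share is zero in every row. If the first length is taken as late as day 3, the day-28 share is (28 - 3)/(91 - 3) = 28%, which changes little.

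**2. Illustration of the bias.** Assumptions, none of them from the documents: growth from birth to 3 months is month-1 growth plus later growth; the two are independent; month 1 supplies a fraction p of the variance; the day-28 measure has correlation r with month-1 growth and no relation to later growth. Then

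spurious correlation = r x sqrt(p).

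With r = -0.2, p = 0.31 gives -0.111, p = 1/3 gives -0.115 and p = 0.45 gives -0.134. A simulation of one million draws at p = 1/3 gave -0.115 for r = -0.2 and -0.232 for r = -0.4. The correlation with growth after month 1 was within 0.002 of zero in both cases; that follows from the independence assumption.

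**3. Would it be noticed?** t = r x sqrt(n - 2)/sqrt(1 - r^2), using the spurious correlation at p = 1/3. Take n = 225 for stool (250 less 10%) and n = 1755 for PHQ-9 (1950 less 10%). The protocol says growth data will be available for all sub-study subjects. PHQ-9 is treated as a score, and the 10% loss is assumed to hold at 3 months.

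| Assumed r | Spurious correlation | abs(t), n = 225 | abs(t), n = 1755 |
|---|---|---|---|
| -0.05 | -0.029 | 0.4 | 1.2 |
| -0.1 | -0.058 | 0.9 | 2.4 |
| -0.2 | -0.115 | 1.7 | 4.9 |
| -0.4 | -0.231 | 3.5 | 9.9 |

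In the stool sample a modest reverse link would usually stay below significance. In the PHQ-9 sample r = -0.1 would be enough.

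**4. Precision of a 1-3 month velocity.** With the same error in each length, velocity error is proportional to 1/interval. The ratio is 91/(91 - 28) = 91/63 = 1.44. A PHQ-9 at day 35 would still fall 7 days into that interval (7/63 = 11%).

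**The case against.** Several points on the other side are sound.

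- **A day-28 measurement is not a day-28 exposure.** Gut inflammation is described as chronic, so the day-28 marker may stand for a state present through month 1, and month-1 growth need not precede the exposure. That stands. But a single sample at the end of the month cannot show which came first, so that part of the interval still cannot support a directional reading.
- **The plan is partly cautious already.** The objective and article 3 speak of association, causality is caveated, and 3-6 month velocity is correctly ordered. These are secondary, non-randomised analyses, and further papers linking milk intake or depressive symptoms to growth are listed as not necessarily part of the PhD. This limits the consequences; it does not correct the birth-to-3-month model, which the Data analysis paragraph still words as an effect.
- **Some details are inferred.** LAZ is mentioned without an age. Its use at 1 month as an outcome of these exposures is possible but not stated. Arm is not named for these regressions, although the same section plans confounder adjustment and interaction terms with cKMC.

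A reader might go further and infer that all three exposures are measured at about day 28. The documents do not support that. Milk intake is measured from about day 4-7 to day 18-21, and stool is also taken at baseline. Both overlap less and lie outside this point.

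**Conclusion.** The point holds for PHQ-9 and the day-28 stool markers against birth-to-3-month velocity. About 31-33% of that interval has passed at measurement, and 38-42% for a PHQ-9 at day 35. If 1-month LAZ is used as an outcome of these exposures, it is contemporaneous with them.

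Two further inferences should be resisted. A third of the time is not a third of the length gained; the documents give no growth share. Nor do they show that any association found would be spurious. The figure of about -0.11 rests on the assumed correlation of -0.2, the assumed one-third share of variance, independence of early and later growth, and no forward effect. It shows that a modest reverse link could matter, above all in the PHQ-9 sample.

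The 3-6 month velocity and every comparison between randomised arms are unaffected. This is a cheap improvement to a secondary analysis.

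**What to change.** **For PHQ-9 and the day-28 stool markers**
- Use length velocity from 1 to 3 months and from 3 to 6 months as the outcomes.
- Adjust for arm, birth weight, gestational age and size at 1 month.
- Do not use 1-month LAZ as an outcome of these exposures.

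**For milk intake and baseline stool**
- Adjust for birth size, gestational age and arm.
- Do not adjust for 1-month LAZ. It follows these exposures and may lie on the pathway to later growth, so adjusting for it could remove part of what is being studied.

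**For all of these models**
- State which stool time point enters each regression.
- Report the exposure-growth results as associations.
- Keep birth-to-3-month velocity for the comparison of arms.

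**Cost.** The change is to the wording of the analysis plan, since lengths at 1, 3 and 6 months are already scheduled. The price is precision: velocity error is about 1.4 times as large over 63 days as over 91. A PHQ-9 taken late in its window still overlaps the 1-3 month interval by up to about a week. A stool sample obtained after the allowed wait overlaps by about 3 days.

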#### 2.5.2 Data gathering method

☒ Other type of intervention

*Specify*

Promotion of, and support for lactation management and skin-to-skin care as soon as possible after birth by study staff in addition to routine visits by government health workers.

☒ Medical examination

*Specify*

Examination for mouth ulcers as these could possibly influence saliva collection

Recording of baby weight and length

Illness identification in baby

Questionnaire-based screening for maternal depressive symptoms at 1 month of baby age

☒ Questionnaire

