## **4.3 Measures**

*Explain any special measures to care for and protect patients/participants in the research project and to limit the potential risks/inconvenience*

Infants who weighed <1500 g, were unable to feed, had breathing problems, were abnormally inactive or excluded for any other reasons, e.g. had major congenital malformations, were referred for care in a hospital. The research team facilitated referral through government health workers who were incentivized to effectuate referral. Problems faced by the mother during the intervention were identified, and mothers helped in resolving these issues using a Counselling Guide. If the mother reported any illness in the infant, referral was facilitated through government health workers.

To reduce the risk of aspiration during saliva specimen collection from the infants, a plastic forceps with “teeth” were used to hold the absorbent swabs. No event of aspiration or even swallowing of the swabs occurred during the trial.

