*Intervention:* The intervention group will receive KMC, i.e. promotion of and support for SSC and EBF as soon as possible after birth by study Auxiliary Nurse Midwives (ANMs) supported by study Accredited Social Health Activists (ASHAs) in addition to the routine postnatal visits by government health workers. The study visits are made daily for the first 3 days, on days 5 and 7,

twice in the second week and once each in weeks 3 and 4. Study ANMs and ASHAs visit together on the first 3 days. Visits will continue till 28 days or till the baby wriggles out. Information on the duration of SSC per day and number of breastfeeds over the last 24 hours will be captured. For any illness, referral will be facilitated through government ASHAs. The babies in the control arm of the trial receive routine postnatal visits by government health workers as implemented through the health system.

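### The optional instrumental-variable analysis cannot isolate skin-to-skin contact or separate it from breastfeeding, because the randomised arm delivers a bundled package

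*Combined protocol and SAP*

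**What the plan says.** The sentence at issue stands in the protocol's data analysis text, under the description of the PhD sub-study. As an optional addition, it proposes "Instrumental Variable analyses to study associations between actual intensity of SSC and Breast feeding and the outcomes". No instrument, model, assumption or sensitivity analysis is given. The sentence before it plans generalized additive models for dose-response between KMC duration and milk volume.

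The protocol's description of the main trial gives one randomised variable, individual allocation to two arms. The intervention arm is described thus: "The intervention group will receive KMC, i.e. promotion of and support for SSC and EBF as soon as possible after birth". The ethics application, section 2.5.2, words it as "Promotion of, and support for lactation management and skin-to-skin care as soon as possible after birth by study staff in addition to routine visits"; those routine visits are the ones that government workers make. Section 4.3 adds that problems mothers met during the intervention were identified and "mothers helped in resolving these issues using a Counselling Guide". For controls, the protocol says: "The babies in the control arm of the trial receive routine postnatal visits by government health workers".

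The SAP covers depressive symptoms and salivary cortisol only. It is by intention to treat and has no IV analysis.

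**The concern.** Arm is a valid instrument for SSC intensity only if it changes the outcome through SSC and by no other route. Here the arm has other routes by design. Lactation management and support for exclusive breastfeeding can act directly on milk intake. Counselling and repeated home visits can plausibly act on maternal mood and stress. Milk intake is measured over 14 days from sub-study enrolment at about day 4 to 7 of life, while support visits are still being made.

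Breastfeeding that SSC itself brings about is a different matter. The protocol's theoretical framework expects that route, and it is mediation, so it does not break the restriction. The violation comes from support, counselling and contact that act other than through SSC.

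At stake is the question the sub-study was set up to answer, namely by which pathways KMC works. An IV figure per hour of SSC would carry the effect of the whole package under the name of one component.

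**Working it through.** The plan states no figure for this analysis, so there is nothing to reproduce. The check covers the visit contrast, the single-exposure estimate and the two-exposure model.

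**1. Visits.** From the intervention paragraph of the protocol: 3 (first three days) + 2 (days 5 and 7) + 2 (week 2) + 1 (week 3) + 1 (week 4) = 9. This is a maximum, because visits may end earlier if the baby wriggles out of the position.

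**2. SSC as the only instrumented exposure.** Inputs:
- Arm difference in milk intake: 60 ml/day (Annexure 3: 0.3 SD, SD 200 ml/day).
- Arm difference in SSC, D: not in the documents. Assumed 4, 8 or 12 hours/day.
- Share s of the arm effect that acts other than through SSC: not in the documents. Assumed 25, 50 or 75%.

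IV (Wald) estimate = 60/D. Effect actually due to SSC = 60(1-s)/D. Ratio = 1/(1-s), whatever D is.

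| D (h/day) | IV estimate (ml per h) | Due to SSC, s = 25% | s = 50% | s = 75% |
|---|---|---|---|---|
| 4 | 15.0 | 11.25 | 7.5 | 3.75 |
| 8 | 7.5 | 5.625 | 3.75 | 1.875 |
| 12 | 5.0 | 3.75 | 2.5 | 1.25 |
| Overstatement | | 1.33-fold | 2-fold | 4-fold |

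The IV estimate is the same along each row: it does not respond to how much of the effect SSC really carries. If the other routes oppose SSC, s is negative and the bias reverses. At s = -25% the ratio is 1/1.25 = 0.80, an understatement.

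**3. Simulation.** With 200,000 dyads, an arm effect of about 60 ml/day, and assumed arm differences of 8 h/day in SSC and 2 feeds/day:

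| True SSC effect (ml per h) | Rest of the arm effect | IV estimate for SSC (ml per h) |
|---|---|---|
| 7.5 | none | 7.48 |
| 3.75 | feeds raised by support | 7.70 |
| 3.75 | other support | 7.45 |
| 0 | other support | 7.52 |

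At this sample size random error is small and the bias remains, so it is not a matter of power. Instrumenting feeds alone fails in the same way. True effects of 0, 15, 0 and 0 ml per feed gave 29.9, 30.8, 29.8 and 30.1.

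**4. SSC and breastfeeding in one model.** Let b_S and b_B be their effects. Two arms give one equation: 60 = 8 b_S + 2 b_B, with the same assumed differences. The pairs (7.5, 0), (3.75, 15) and (0, 30) all satisfy it: 8 × 7.5 = 60; 8 × 3.75 + 2 × 15 = 60; 2 × 30 = 60. Formally, the instruments (constant, arm) against the regressors (constant, SSC, breastfeeding) give a moment matrix of rank 2 where 3 is needed. The separate effects are not identified, even if every other assumption held.

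**The case against.** The strongest reply is that this is one permissive sentence. No objective, hypothesis or listed outcome concerns SSC intensity, the sentence speaks of associations, and the protocol concedes several times that causality may be hard to establish. The pairing of SSC with breastfeeding can also be read as one composite, since the introduction names both as key components of KMC. Arm as instrument is an inference.

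Much of this stands, and it limits the point to an optional analysis. It does not make an SSC-specific IV estimate valid. The usual reason for using an instrument is to obtain a causal effect, and the general caveats address neither the exclusion restriction nor the separation of two exposures. If a composite is meant, the text should say so.

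Four stronger readings are tempting but not supported:
- **That controls had no study attention.** In the milk-intake subsample, both arms have sub-study contacts at enrolment, on days 1, 3, 7, 13 and 14 after it, and at age 28 days. The contrast is the extra support visits, and these common contacts do not remove it.
- **That the IV estimate must be too large.** That needs the other routes to act in the same direction as SSC. The ethics application, section 4.2, notes that lengthy visits tired a few women, so an opposing route cannot be ruled out.
- **That SSC is not recorded in controls.** Its capture is described only within the intervention paragraph, but section 2.3.2 of the application lists KMC adoption without restricting it to one arm, and the main-trial protocol is not among the documents. This is a point to state, not a shown defect.
- **That a causal effect per hour of SSC is planned.** The text does not say so.

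**Conclusion.** The concern holds for the optional IV analysis only. With arm as the instrument, an estimate for SSC alone would be a package effect divided by a difference in SSC hours, and separate SSC and breastfeeding effects cannot be identified from one binary instrument. The bias factor is 1/(1-s), or 1.33 to 4 for assumed shares of 25 to 75% acting in the same direction as SSC. It falls below 1 if the other routes oppose SSC, and sample size does not reduce it. The conclusion rests on arm being the instrument, which is inferred because it is the only randomised variable. Arm-by-covariate interactions could in principle supply more instruments. They would need exposure effects that do not vary with those covariates and no direct effect of support, and the documents plan nothing of the kind.

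A reader might infer that the main results are compromised. They are not: every intention-to-treat comparison estimates the effect of ciKMC as delivered, which is how the hypotheses and objectives are framed. Nor does the SAP for depressive symptoms and cortisol carry the IV proposal forward. For milk intake and gut markers, the documents contain no later plan that withdraws it.

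**What to change.** Amend the IV sentence in the protocol's data analysis text:
- State that separate IV effects of SSC and of breastfeeding will not be reported.
- If IV is used, name randomised arm as the instrument and define a single exposure, uptake of the ciKMC package, recorded in the same way in both arms. State the assumption that arm acts only through that uptake, and label the result the complier effect of the package.
- Report SSC-hours dose-response results, including those from the generalized additive models, as observational associations.

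The cost is a wording change, plus confirmation of how uptake was recorded in controls. What is given up is a causal per-hour SSC estimate, which this design cannot support.
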